### Follow-up

2.6

At the end of each course of treatment, patients must return to the hospital for a visit. If necessary and the patient wishes, the trial procedure for the next course of treatment can be started. At the same time, visits must be made every 3 months after each course of treatment. Visits and examinations include blood routine, blood biochemistry, urine routine, stool routine, and coagulation function test on accompanying medications. Carcinoembryonic antigen (CEA) and other tumor markers, CD antigen, T cell activity assessment, vital signs, ECOG score, electrocardiogram, imaging examination (CT, MRI). Please refer to the visit plan for details of the visit plan (**Table 1**). When a certain assessment is required, a “ √ ” will be marked on the visit plan.

**Table 1 T1:** Visit reporting table.

Item	The end of treatment	Post-treatment visit (every 3 months)
Concomitant medication	✓	✓
Blood routine	✓	✓
Blood chemistry	✓	✓
Urine routine	✓	✓
Bowel routine	✓	
Coagulation function test	✓	
Thyroid function test	✓	
Alpha-fetoprotein	✓	
Pregnancy test	✓	
Vital signs	✓	✓
Physical examination	✓	✓
ECOG score	✓	✓
Electrocardiogram	✓	
Echocardiogram	✓	
Blood pressure detection	✓	
Film degree exam	✓	

The follow-up plan lasts for 24 months and is divided into 8 times, that is, every 3 months after the end of treatment, 10 mL of blood will be collected each time for efficacy and safety evaluation, while compliance will be assessed and combined medication status will be recorded.

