### Study design

2.2

The trial is an open-label, multicenter randomized phase II study (**Figure 1**), which includes 2 of the following queues:

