**Figure 1 f1:**
[figure not shown]
Flowchart of the study design.

**Control group:** placebo + conventional treatment (including radiotherapy) group,

**Intervention group:** personalized tumor peptide vaccine + conventional treatment (including radiotherapy) group,

Subjects will be stratified according to different cancer types and first, second, and third-line treatment stages based on individual condition assessment, and then randomly enter two cohorts in a 1:1 ratio. In addition, there is a one-way crossover experiment (cross-over design) during the research process. Cross-over to the investigational treatment arm (peptide vaccine plus radiotherapy) will be permitted only for patients in the control group who demonstrate radiologically confirmed disease progression, as assessed by RECIST 1.1 and verified by the investigator. Eligibility for cross-over requires that patients meet predefined safety and clinical criteria, including an ECOG performance status of ≤2, absence of Grade ≥3 adverse events, and adequate hematologic, hepatic, and renal function. The proportion, timing, and reasons for cross-over will be systematically recorded and transparently reported. The intervention group will undergo the second phase of personalized tumor peptide vaccine group plus conventional treatment (including radiotherapy), and the response rate of the two phases will be evaluated before and after crossover. In both cohorts, all subjects received radiotherapy, and radiotherapy doses will be further divided into low and high doses. This design will allow us to answer questions about vaccination efficacy and the impact of various radiation doses.

For patients who want to enroll in neoantigen clinical trials, screening for neoantigens may be recommended. It is necessary to take the patient’s fresh tumor tissue (surgery or biopsy or cerebrospinal fluid, pleural effusion, ascites, etc.), and perform whole-exome and whole- transcriptome sequencing on peripheral blood for further clinical development of individualized targeted treatment plans. At the same time, these test data can be used for personalized tumor neoantigen screening in this study. Peptide vaccine therapy requires an 8-week preparation period for the preparation of the peptide vaccine, during which patients continue to maintain standard treatment.

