Patients entering the control group’s conventional treatment (including radiotherapy) group will receive conventional treatment plus radiotherapy. Radiotherapy is divided into low-dose and high-dose (first phase); until disease progression occurs, patients can choose to “cross groups” and receive individual treatment. The second stage of treatment consists of tumor peptide vaccine plus radiotherapy (no harm from treatment in the early stage). Patients entering the intervention group ‘s individualized tumor peptide vaccine + conventional treatment (including radiotherapy) group will complete three precise radiotherapy sessions before initiating vaccination with the peptide vaccine. The peptide vaccine treatment will be carried out one week after the end of radiotherapy. The peptide vaccine treatment will last for 5 months. It is a course of treatment until the treatment discontinuation event specified in the protocol occurs. Subjects will continue to undergo post-treatment safety visits, survival follow-ups and tumor progression follow-ups after finishing treatment.

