#### Primary study endpoints

2.5.1

Progression-free survival (PFS): (Evaluation index: RECIST 1.1, with inclusion of FDG-PET/CT).

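### The visit table schedules no scan after end of treatment although PFS is primary, and visits run from the end of a course that is undefined for controls, so equal scan timing is not assured

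*Protocol article*

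**What the plan says.** All references are to the protocol article.

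- **Endpoint.** Section 2.5.1 makes PFS primary, with "Evaluation index: RECIST 1.1, with inclusion of FDG-PET/CT". Section 2.9 restricts it to data from before cross-over. Table 2 in section 2.8 counts PFS events to month 36.
- **Visits.** Section 2.6 states that "visits must be made every 3 months after each course of treatment". Its list of visit examinations includes "imaging examination (CT, MRI"; FDG-PET is not named there. The text then refers to Table 1 and says that a tick marks a required assessment.
- **Table 1.** There are two columns: end of treatment, and the 3-monthly post-treatment visit. The row "Film degree exam" is ticked in the first and blank in the second. The paragraph after the table plans 8 visits over 24 months and names only a blood sample.
- **After treatment.** Section 2.2 nevertheless says that subjects continue to be followed for tumour progression once treatment has finished.
- **Course length.** "The peptide vaccine treatment will last for 5 months" (section 2.2). Radiotherapy takes 1 week in either arm (section 2.3.1). No control course is given.
- **Control and masking.** "The trial is an open-label, multicenter randomized phase II study", yet the control arm is "placebo + conventional treatment (including radiotherapy) group". Section 2.8 glosses placebo as standard care, and section 2.3 contains no placebo procedure.
- **Cross-over.** Controls may cross over on radiologically confirmed progression, "as assessed by RECIST 1.1 and verified by the investigator".

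**The concern.** PFS dates are scan dates. If the document that tells sites what to do asks for no scan after end of treatment, progression in follow-up is found only through unscheduled imaging or not at all, and those dates cannot be recovered later.

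The anchor is a second weakness. A clock that starts at the end of a course gives the two arms the same calendar only if their courses have the same length. With different calendars, the arm scanned later has its progressions recorded later, and a PFS difference can appear without any vaccine effect. The document does not let a reader rule this out.

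The trial is also open-label, and the investigator verifies the progression that opens access to the vaccine for controls. A progression date left open until after that decision is exposed to knowledge of the arm.

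**Working it through.** **1. The plan's own figure.** Inputs from section 2.8: medians 4 and 8 months (HR 0.50), two-sided α 0.025, power 80%, 1:1 allocation, uniform accrual over 24 months, 36 months in total, loss 0.10.

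- Events (Schoenfeld): 4(2.241 + 0.842)² / (ln 0.5)² = 79.1, so 80.
- Event probability per arm: h/(h+λ) × [1 − exp(−(h+λ)u)], averaged over follow-up u from 12 to 36 months, with h = ln 2/median. Reading the loss as 10% per month, λ = −ln 0.9, this gives 0.619 and 0.442.
- At 77 per arm: 77 × 0.619 + 77 × 0.442 = 47.6 + 34.0 = 81.6 events. Table 2 has 47.7 + 33.9 = 81.6.

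The sample size reproduces. It presumes that progression is observed up to month 36.

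**2. Table against text.**

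| Place | Imaging after end of treatment |
|---|---|
| 2.2 | progression follow-up planned, no timing |
| 2.6, text | CT and MRI in the list of visit examinations |
| 2.6, Table 1 | imaging-like row blank |
| 2.8, Table 2 | PFS events counted to month 36 |

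Treating the row as imaging is an inference from its label. If it is not imaging, Table 1 requires no scan at all.

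**3. When the anchor falls.** Vaccine arm: 1 week of radiotherapy + 1 week interval + 5 months of vaccination = about 5.5 months from the start of radiotherapy. Control arm: not stated.

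**4. Two possible cases.** The scan times below are assumptions.

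*Case A: the calendars differ.* Simulation with no true effect: median 4 months in both arms, 77 per arm, progression recorded at the next scan, censoring at the last scan, scans 3-monthly after the first, 1,000 runs per cell. Loss is 10% in total or 10% per month. The table shows the share of trials significant in favour of vaccine; nominal is 0.025/2 = 1.25%.

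| First scan, control / vaccine (months) | 10% in total | 10% per month |
|---|---|---|
| 0.25 / 5.5 | 6.4% | 10.1% |
| 3 / 5.5 | 2.8% | 5.0% |
| 3 / 3 (shared) | 1.7% | 1.2% |
| 5.5 / 5.5 (shared) | 0.8% | 1.2% |

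Monte Carlo error is at most about 1 percentage point. The shared calendars are compatible with nominal; the unequal ones give roughly 3% to 10%.

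*Case B: both arms are first scanned at about 5.5 months.* Progressed by then on the planned medians: controls 1 − 2^(−5.5/4) = 0.61; vaccine 1 − 2^(−5.5/8) = 0.38. More than half of controls have progressed before anyone looks, so a 4-month median cannot be observed. There is no false-positive inflation in this case.

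**The case against.** **The article condenses a fuller protocol.** Table 1 has no baseline or on-treatment column, and scans during the 5-month course may be set elsewhere. This stands. A reader might infer that the first scan is at 5.5 months; the document does not establish that, so case B is conditional. It does not rescue the post-treatment column, which the table covers and leaves blank.

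**The text does not assign CT and MRI to the 3-monthly visits in particular.** The list covers both visit types and defers to the table; stool, coagulation and ECG tests are in the same list and are also ticked only at end of treatment. This softens the clash between text and table. It leaves the clash with the planned progression follow-up and with events counted to month 36.

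**A reader might infer that the course differs by arm.** Section 2.2 describes controls as receiving conventional treatment plus radiotherapy, which points that way. But that treatment is described as running until progression, and the arm is labelled placebo. If placebo mirrors the vaccine schedule, timing is equal. What is established is only that the control course is undefined.

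**A reader might add the two harms together.** They need incompatible control schedules: early scans in case A, a first scan at 5.5 months in case B.

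**The simulated rates depend on convention.** With controls scanned from 0.25 months and loss of 10% per month, censoring at drop-out instead of at the last scan takes the rate above 20%. The figures show direction and rough size, not a forecast.

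**A reader might infer that investigators will call control progression early.** The incentive exists, but the document gives no rate for it, so no size is attached. It requires radiological confirmation, and it does not say that whoever verifies cross-over also sets the PFS date. Investigator assessment in an open-label phase II trial is a design choice.

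**Conclusion.** The point holds in a limited form. Table 1, followed as written, schedules no imaging after end of treatment, which cannot support PFS counted to month 36; this rests on reading one translated row label as imaging. Visits are anchored to the end of a course instead of randomisation, and the control course is undefined, so equal scan timing is not assured.

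The consequence depends on facts not stated: roughly 3% to 10% false positives favouring vaccine against 1.25% if controls are scanned earlier than vaccine patients; an unobservable control median, with 61% already progressed, if both arms wait until about 5.5 months; neither if a shared calendar with on-treatment scans exists in the full protocol. The sample-size figures are not wrong on this point.

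The open-label and placebo descriptions conflict, and the statement in section 3.2 that the evaluation is free of inherent bias goes further than an unmasked design allows.

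**What to change.** 1. Tick imaging at every 3-monthly visit in Table 1, and name the row plainly as tumour imaging.
2. Schedule tumour assessments from randomisation, in the same weeks in both arms, at intervals no longer than the plan's own 3 months, until progression whatever the treatment status.
3. Reconcile the open-label description with the placebo label and with the gloss of placebo as standard care. If the trial is unmasked, remove the freedom-from-bias claim in section 3.2.
4. Record and lock the progression date before cross-over is authorised.

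Reading of scans by someone unaware of the arm would help, but it is a suggestion only: the document names no such reader, so its cost cannot be judged from here.

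The cost of items 1 to 4 is a corrected table, some wording, and a few scans moved onto a fixed calendar. Recruitment began in January 2024, so scan dates of patients already enrolled should be kept as they occurred and the new calendar applied to their remaining assessments.

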### Security monitoring

2.7

#### Adverse events

2.7.1

Investigators should record all adverse events that occur during drug treatment in a case report form (CRF).

An adverse event refers to any unfavorable change that occurs after taking the study drug or control drug compared with the patient’s baseline (before treatment), including recurrence of other original diseases that occur during the clinical study, regardless of whether its occurrence is related to treatment. Clinically performed invasive examinations themselves are not considered adverse events, but the causes leading to these examinations should be.

Regardless of whether the patient is voluntary or not, all adverse events discovered by investigators, physical examinations, laboratory tests or other methods should be recorded in the CRF “Adverse Event Table”, and treatment and recording should be carefully tracked until recovery. Abnormal laboratory test results alone are generally not considered adverse events unless they are accompanied by clinical symptoms, signs, or require treatment.

When completing the CRF Adverse Event Page, the severity of each adverse event should be appropriately assessed:

1. Duration (start and end dates);2. Severity: Adverse reactions are classified according to the following criteria according to the most severe degree:3. Mild: Easier to tolerate, causing only mild discomfort and not affecting daily activities.4. Moderate: Causes significant discomfort and affects daily activities.5. Severe: unable to perform daily activities.

Causal relationship to investigational drug:

1. Definitely related: The occurrence of this reaction is consistent with the known reaction type of the suspected drug; it is consistent with the reasonable sequence of events after taking the drug. The adverse reaction is reduced or disappears after the drug is reduced or discontinued, and the same reaction occurs again after the drug is reused.2. Possibly related: the reaction conforms to the known reaction type of the suspected drug; it conforms to a reasonable time sequence after taking the drug, and the adverse reaction is reduced or disappears after reducing or discontinuing the drug, but the patient’s clinical status cannot reasonably explain the reaction.3. Possibly related: The reaction is consistent with the known reaction type of the suspected drug; it is consistent with the reasonable time sequence after taking the drug, and the patient’s clinical status or other treatment methods may also produce this reaction.4. Unlikely: A clinical event, including abnormal laboratory tests, is temporarily related to the time of drug taking, and other drugs, compounds, or the patient’s underlying disease can provide a more reasonable explanation for the event.5. Unable to evaluate: The information displayed in the adverse event report is insufficient or contradictory, and the information in the report cannot be supplemented or corrected, so it cannot be judged.6. Irrelevant: It does not conform to the known reaction type of the suspected drug; it does not conform to the reasonable time sequence after taking the drug, and the patient’s clinical status or other reasons can explain the reaction.

The treatment measures and outcomes of adverse events should be recorded on the CRF form. All adverse events should be followed until resolution or stabilization.

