#### Secondary objectives

2.1.2

The secondary objectives to observe and evaluate the safety of combined peptide vaccines under different radiotherapy doses, and to evaluate the impact of RT dose on the immunogenicity of peptide vaccines on local radiotherapy field response and distant response rate.

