### Treatment methods

2.3

This study includes personalized neoantigen peptide vaccine treatment and precision radiotherapy. The treatment sequence is radiotherapy first and then vaccine (**Figure 2**). The interval between precision radiotherapy treatment and peptide vaccine is 1 week.

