#### Precision radiotherapy

2.3.1

The course of treatment is 1 week, 3 times in total.

1. Critical lesion eliminating radiation therapy CLERT, in accordance with isotoxicity planning, radiation dose limits are based on standard NCCN (National Comprehensive Cancer Network) guidelines recommended for organs at risk (Organs at risk, OAR) limit dosage to 80% formulation.2. Critical lesions (Critical lesions) are defined as tumors in critical locations. If the tumor progresses in this location, it will lead to the patient’s death or severe symptoms, affecting the patient’s QOL (the quality of life). Life-threatening tumors such as: central lung cancer; tumors adjacent to large blood vessels, large tracheas, heart, esophagus and other mediastinal tumor lesions; metastatic tumors located in or adjacent to the brainstem. Situations that seriously endanger QOL include, but are not limited to, the following situations: tumors are in the spinal cord, esophagus, portal area, and load-bearing bones, or are close to the rectum, bladder, etc. The final decision was made by a panel of on-study radiation therapy experts.3. Radiotherapy, SBRT (stereotactic body radiation therapy), the protocol is 8–10 Gy × 3 versus 2 Gy × 3. The radiation dose limit is based on 80% of the OAR limit dose recommended by the standard NCCN guidelines. If the metastases are close to important structures such as the brainstem or esophagus, or have been previously treated with radiotherapy, the radiation dose limit allows the SBRT radiation dose to be adjusted to the OAR guideline limit dose.4. The key tumor is the treatment target area, which refers to the tumor tissue that mainly affects or threatens the patient’s life or QOL, regardless of the primary site or metastasis, as mentioned above. EDIC (The effective dose to the circulating lymphocyte EDIC, the equivalent dose of circulating lymphocytes) is an important reference indicator for formulating radiotherapy plans. The EDIC is limited to an effective dose that produces grade 2 or higher lymphocyte deficiency in less than 5% of patients. (Patented, part of the research data was disclosed by [name]/[name], et al. in ASTRO2017).

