#### Secondary study endpoints

2.5.2

Incidence and severity of adverse events among all treated subjects (evaluation indicators: Treatment toxicity graded according to CTCAE 5, Common Terminology Criteria for Adverse Events 5; overall survival (OS); objective response rate (ORR); In-field response to local radiotherapy; Distant response rate.

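### The adverse event section conflicts with the safety endpoint and the safety objective on how events are graded and when collection starts

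*Protocol article*

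**What the plan says.** **Collection and definition (section 2.7.1).** The instruction is: "Investigators should record all adverse events that occur during drug treatment in a case report form (CRF"). The definition that follows is: "An adverse event refers to any unfavorable change that occurs after taking the study drug or control drug", judged against baseline and regardless of relationship to treatment. Radiotherapy is not named as a starting point.

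**Severity (section 2.7.1).** The CRF adverse event page has three levels. The highest reads "Severe: unable to perform daily activities".

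**Causality (sections 2.7.1 and 2.7.2).** Both rate the relationship to the investigational drug only.

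**Laboratory findings (section 2.7.1).** "Abnormal laboratory test results alone are generally not considered adverse events unless they are accompanied by clinical symptoms, signs, or require treatment".

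**What these data must serve.** Section 2.5.2 sets the secondary safety endpoint in all treated subjects: "Treatment toxicity graded according to CTCAE 5". Section 2.1.2 includes the aim to "evaluate the safety of combined peptide vaccines under different radiotherapy doses". Section 2.2 requires a control patient who crosses over to be free of events of Grade 3 or above. Section 2.4.3 gives cytokine release syndrome at level 4 as an example of an adverse reaction that ends study treatment.

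**Treatment order (sections 2.2, 2.3 and 2.3.1).** "The treatment sequence is radiotherapy first and then vaccine". Radiotherapy takes one week, and the interval to vaccination is one week.

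**The concern.** A safety endpoint can report only what the CRF collects. An investigator who follows section 2.7.1 literally will enter one of three severity words, start at the first dose of study or control drug, and judge each event against that drug alone. The endpoint and objective need CTCAE grades, the period in which radiotherapy is given, and a way to tell radiotherapy toxicity from a vaccine reaction.

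Three things are at stake. The tabulation by CTCAE grade would rest on a scale that does not carry those grades. The comparison of 8–10 Gy × 3 with 2 Gy × 3 would miss the weeks in which an acute toxicity difference could first appear. Radiotherapy effects that surface after vaccination could be counted as vaccine reactions. Recruitment began in January 2024, and events not recorded at the time are hard to recover later.

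**Working it through.** The article gives no safety figure to reproduce. The check sets the sections side by side; the only arithmetic is the length of the period before the first vaccine dose.

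**1. Grading scale.**
- Collected (2.7.1): mild, moderate, severe.
- Required (2.5.2): CTCAE 5 grades. Also used: Grade 3 or above (2.2) and level 4 (2.4.3).
- The top CRF level is defined by inability to carry out daily activities. No level is set aside for life-threatening or fatal events, so Grades 3, 4 and 5 share one category and cannot be recovered from it.
- Section 2.7.2 lists fatal or life-threatening events as serious and records severity and outcome, but it does not ask for a CTCAE grade.

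**2. Start of the window in vaccine patients.**
- Radiotherapy course (2.3.1): 1 week.
- Interval to vaccine (2.3): 1 week.
- Time from start of radiotherapy to first vaccine dose: 1 + 1 = 2 weeks, all before any study drug.
- Section 2.3.2 appears to mean that vaccination starts within one week of the end of radiotherapy. On that reading the period is between 1 and 2 weeks. Either way the whole radiotherapy course lies outside the definition.
- Toxicity that first appears after the first dose is inside the definition, because relatedness is not required.

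**3. Start of the window in controls.**
- The abstract and the arm definitions in 2.2 give controls placebo, which can serve as the control drug that opens the window.
- The later account of control treatment in 2.2 mentions conventional treatment and radiotherapy but no placebo. If that account is followed, no control drug marks the start.

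**4. End of the window.**
- 2.7.1 refers to the drug treatment period.
- 2.2 plans safety visits after treatment, and 2.6 plans 8 visits over 24 months (24 ÷ 8 = every 3 months), with blood taken partly for safety.
- The two do not agree on when collection of new events stops.

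**5. Attribution.**
- Causality is rated to the investigational drug only. The third causality category covers events that the patient's condition or another treatment could also explain, which fits radiotherapy toxicity, and it is labelled as possibly related.
- Section 2.9 counts possibly related events as adverse reactions. A radiotherapy effect appearing after vaccination can therefore enter that count, with no field to separate it.

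**6. Laboratory events.**
- 2.7.1 generally leaves symptom-free laboratory abnormalities off the adverse event page, while 2.3.1 shows that lymphopenia matters to the radiotherapy plan: "The EDIC is limited to an effective dose that produces grade 2 or higher lymphocyte deficiency in less than 5% of patients".
- Table 1 schedules routine blood counts at the end of treatment and every 3 months. If these include a differential count (an assumption), lymphocytes at those visits can be graded without new tests.

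**The case against.** The strongest reply is that the article does promise CTCAE 5 grading in all treated subjects, so section 2.7.1 may be loosely worded general text that the trial will not follow literally. Serious events have their own route in 2.7.2, which is not expressly tied to the drug period and identifies fatal and life-threatening cases. Leaving clinically silent laboratory values off the adverse event page is a common convention.

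Much of this stands, and it rules out several stronger readings that a reader might infer:

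- *That events are recorded only during drug treatment and late radiation effects are lost.* The text does not say only. Post-treatment safety visits are planned, events are followed to resolution or stabilisation, and late effects fall after the drug, so they meet the definition.
- *That the CTCAE endpoint cannot be obtained.* Section 2.5.2 prescribes it. The documents show a conflict, not an impossibility.
- *That controls have no adverse event collection.* This requires setting aside the placebo named in the abstract and in 2.2.
- *That symptom-free lymphopenia would count as zero, leaving the 5% limit uncheckable.* The exclusion is qualified by the word generally, blood counts are scheduled, and the 5% figure constrains radiotherapy planning; it is not a trial endpoint.
- *That the cross-over check has no data source.* Nothing says it must be drawn from the adverse event page.
- *That the repeated causality label distorts results.* Categories 2 and 3 share a label, but their definitions differ and 2.9 pools them.

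What the reply does not answer is that 2.7.1 is the instruction for completing the CRF, and on scale and start it says something different from the sections that depend on it. Non-serious acute radiotherapy toxicity before the first dose has no stated route.

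**Conclusion.** The point holds as an internal contradiction. Section 2.7.1 conflicts with 2.5.2 on the severity scale and does not cover the radiotherapy period that 2.1.2 needs. Followed as written, it merges Grades 3 to 5, leaves about 2 weeks before the first vaccine dose outside the definition (between 1 and 2 weeks if vaccination may start sooner), and gives radiotherapy no attribution of its own. The end of the window is stated inconsistently, and the start in controls is unclear only if the account without placebo is the one followed.

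This rests on investigators completing the CRF as 2.7.1 tells them to, and on the stated radiotherapy course and interval. It does not show that the safety endpoint is lost. CTCAE grades and acute pre-vaccine toxicity are not reliably captured, and this should be corrected while patients are still being enrolled.

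**What to change.** 1. Replace the three-level scale on the CRF adverse event page with CTCAE 5 grades 1 to 5.
2. Collect adverse events in both arms from the same start point, either randomisation or the first radiotherapy fraction, through the planned follow-up visits, and amend the definition in 2.7.1 to match.
3. Record attribution to radiotherapy and to the vaccine in separate fields.
4. Grade lymphocyte counts by CTCAE from the blood counts already taken.
5. Reconcile the two descriptions of control treatment in 2.2, so that the start of collection in controls does not depend on which one is read.

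The cost is a CRF revision, protocol wording and slightly more data entry; no new tests are needed. For patients already treated, events from the radiotherapy period and CTCAE grades would have to be taken from source records where these allow. None of this changes a dose, a schedule or a treatment rule.
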